**Study procedures (clinical):** The study population would include patients with chemoresistant oral cancers, fit for MCT-E. In stage 1, a dose de escalation design with continuous reassessment model would be used to identify OBD of methotrexate. The disease control rate at 2 months and the proportional decline in CECs would be used for decision making regarding de escalation. Around 20-30 patients would be required for stage 1. In the second stage the combination of MCT-E would be administered in 76 patients. These patients would be followed at 8th day then subsequently every 30th day till death.

Disease progression would be defined as per RECIST criteria version 1.1. Serum and tissue biopsy would be collected in all patients at baseline prior to the start of MCT-E, at day 8 and at progression. In addition serum samples will be collected at monthly intervals till progression for serial assays of serum biomarkers.

**Study procedures (laboratory):** CECs would be measured in serum by flow cytometry. The other serum angiogenesis related markers would be quantified by ELISA. The tissue tumor immunity and angiogenesis markers would be measured by immunohistochemistry. Microarray would be used to profile the gene expression profile in the tumor specimens. PK/PD would be studied by plasma methotrexate drug level analysis.

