| Study procedure          | 
Intervention : Patients would receive the intended oral therapy
These patients would be monitored for response and toxicity (CTCAE version 4.02) at D8 and D30. Following which they would be assessed every month.
 
Biomarker : All patients would undergo serum biomarker investigations at least 1 day before administration of oral therapy, then at at D8, D30 and for next 3 months
 
Biopsy : Done at baseline, then at at D8 and at progression.
 
Response (Radiology) : Done at baseline and then at 1 monthly intervals
                                                              |
| Sample Size              | Around 20-30 patients would be required for stage 1. In the second stage the combination of MCT-E would be administered in 76 patients.                                                                                                                                                                                                                                                                                                                                                                                                                                                                                                                |
| Date of first enrollment | Post IRB/IEC and grants approval.                                                                                                                                                                                                                                                                                                                                                                                                                                                                                                                                                                                                                      |

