### 12.2 Laboratory interventions

#### Sample collection:

1. **Tumor tissues will be collected at baseline ( +1 month prior to 2 days post MCT start), C1D8 (+/- 2 days) and at progression.** Fresh(~20-30 mg) and formalin fixed tumor tissues will be used. Tumor content will be assayed and tissues having less than 60% of tumor will not be used for microarray analysis. Fresh tumor tissue will be subjected to extraction of DNA and total RNA while fixed tumor tissues will be used for IHC.
2. **20 ml of blood will be collected (5 ml in 3 EDTA tube and 5 ml in plain tube) at baseline collected at baseline ( +7 days prior to 1 days post MCT start) , C1D8(+/- 2 days) and at progression.** 1 EDTA tube each will be used for Flow cytometry, Microarray and ELISA. Fourth tube will be a reserve. 10 ml of blood will be used for separation of plasma (5 ml) and serum (5ml) which will be stored at -80°C, used for analysis of various parameters.
  - a. PK-PD Sample size collection restricted to stage 1
    - i. 5 ml blood will be collected at each time point. Immediately after collection, blood samples will be kept on ice till they are further process to separate plasma by centrifugation at 4°C. Plasma samples will be stored

at -80°C till further analysis of drug levels (Bioanalysis using LC-MS/MS) and levels of CECs and biomarkers.

| DRUG         | TIME POINTS FOR SAMPLING            | No. of Draws | Cycle and Day |
|--------------|-------------------------------------|--------------|---------------|
| Methotrexate | 0, 0.5, 1, 1.5 , 4, 6, 8, 24, 30 hr | 9            | C1D1,         |

3. **At the time of each monthly D30 (+/- 7 days) follow up 10 ml of blood will be collected in EDTA tube for the first 3 months for Flow cytometry and ELISA .**

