### Flow cytometry procedure

#### Timeline for doing flow cytometry

All patients would undergo serum CEC/EPC at least 4 day before administration of oral therapy, then at at D8 (+/- 2 days) , D30 (+/- 5 days), 30 days interval for first 3 months (+/- 7 days) and at progression.

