### Need for multiple biopsies

This genomic analysis will help us to understand the mechanism of action, pathways involved in response and resistance. Three biopsies are required. The reason for these biopsies are

1. The baseline biopsy will help us understand about gene expression in platinum insensitive oral cancers, which genes are upregulated and which are down regulated. This information can not help us in understanding mechanism of action. As the drug exposure has not yet happened. It will gives the baseline state of gene expression in platinum insensitive oral cancers.
2. The biopsy on next visit that is 7th day will then be taken and a gene expression analysis will be done. This gene expression analysis will be compared with the baseline gene expression analysis. This would tell us that after exposure to this combination of MCT\_E which genes are upregulated and which are down regulated. This information will then be used to derive pathways which are upregulated or downregulated post exposure to metronomic chemotherapy. So base on these two biopsies we would get the pathways which are activated or deactivated by MCT ie mechanism of action.

- a. The day 7 biopsy is selected as metronomic molecular actions are genetically expressed by day 6.
3. Now that we would know which pathways are helpful in metronomic action. We would do the third biopsy at progression. The comparison of gene expression of third biopsy would be done with the second one. This will tell us which pathways are responsible for resistance

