## 13 Time and Events Table

All baseline investigations should be performed prior to the start of the chemotherapy. Hematological and biochemical investigations should be obtained within one week of start of chemotherapy. Imaging investigations may be performed within 2 weeks of the start of chemotherapy. All investigations indicated on the chart below will be repeated on the day of the chemotherapy prior to the administration of the chemotherapy.

| Day                                                       | Pre-study | C1D1 | C1D8 | D1 of first 3 cycles | D1 of subsequent cycles | Progression |
|-----------------------------------------------------------|-----------|------|------|----------------------|-------------------------|-------------|
| Eligibility Screen                                        | ✓         | -    | -    | -                    | -                       | -           |
| Informed Consent                                          | ✓         | -    | -    | -                    | -                       | -           |
| Multi speciality Board                                    | ✓         | -    | -    | -                    | -                       | -           |
| History                                                   | ✓         | -    | ✓    | ✓                    | ✓                       | ✓           |
| Physical Examination                                      | ✓         | -    | ✓    | ✓                    | ✓                       | ✓           |
| Toxicity Charting                                         | -         | -    | ✓    | ✓                    | ✓                       | ✓           |
| Complete Hemogram                                         | ✓         | -    | ✓    | ✓                    | ✓                       | ✓           |
| Renal Function                                            | ✓         | -    | ✓    | ✓                    | ✓                       | ✓           |
| Liver Function                                            | ✓         | -    | ✓    | ✓                    | ✓                       | ✓           |
| Serum Electrolytes (Ca 2+ / Mg 2+ ) | ✓         | -    | ✓    | -                    | -                       | -           |
| Biopsy                                                    | ✓         | -    | ✓    | -                    | -                       | ✓           |

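### Protocol section 12.2 lets baseline blood and tissue be taken after treatment has started, against the protocol's other baseline rules, so the Stage 1 CEC baseline is not fixed as pre-dose

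*Protocol*

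**What the plan says.** **The collection rule.** Protocol section 12.2, Sample collection, sets two baseline windows.

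- Item 1, tissue: "Tumor tissues will be collected at baseline ( +1 month prior to 2 days post MCT start".
- Item 2, blood: "at baseline collected at baseline ( +7 days prior to 1 days post MCT start". On the use of that draw: "1 EDTA tube each will be used for Flow cytometry, Microarray and ELISA". Flow cytometry is the CEC assay; the Summary (section 2) states "CECs would be measured in serum by flow cytometry".

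**The other baseline rules.**

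- Section 2, Summary: serum and biopsy at baseline both precede the start of treatment.
- Section 3, Concept sheet: "All patients would undergo serum biomarker investigations at least 1 day before administration of oral therapy". For the biopsy it says only that one is done at baseline.
- Section 12.2, Timeline for doing flow cytometry: "All patients would undergo serum CEC/EPC at least 4 day before administration of oral therapy".
- Section 12.2, Need for multiple biopsies, on why the baseline biopsy cannot show mechanism of action: "As the drug exposure has not yet happened".
- Section 13: "All baseline investigations should be performed prior to the start of the chemotherapy". Its calendar (Table 7) ticks biopsy and serum markers under the pre-study column and not under C1D1.

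**Where the baseline is used.** Sections 15 and 16.1 make the proportional decline in CECs, measured at day 8 of cycle 1, a twin Stage 1 primary endpoint with clinical benefit at 2 months. Section 4.7 sets the deciding decline at more than 10%, because CEC measurement varies by up to about 10%.

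**The concern.** Methotrexate, erlotinib and celecoxib all begin on D1 (Table 3). Blood drawn one day after the start, or tissue taken two days after, is therefore an on-treatment sample. The protocol partly treats it as such: in Stage 1, section 12.2 schedules draws up to 30 hours after the C1D1 dose, including one at 24 hours. These are for drug levels and for CECs and biomarkers as pharmacodynamic measures. A 24-hour sample is thus a drug-response measurement under one sub-item and an acceptable baseline under the item that contains it.

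Three comparisons depend on a clean baseline:

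- the Stage 1 CEC decline, where the baseline is the denominator;
- the change in the ELISA markers;
- the baseline-to-day-8 gene expression contrast, which the protocol reads as mechanism of action because the first biopsy is taken to be unexposed.

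The CEC cut-off is of the same order as the stated measurement variation, so a modest shift in the denominator could move a patient across it. Once a sample has been taken late, the pre-dose value cannot be recovered.

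**Working it through.** The protocol gives no figure for this point to reproduce. The check compares the windows and then illustrates what a shifted denominator does.

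**1. Windows in days from treatment start (D1 = day 0)**

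| Source | Blood / CEC baseline | Biopsy baseline |
|---|---|---|
| 12.2 Sample collection | -7 to +1 | -1 month to +2 |
| Section 2 Summary | before start | before start |
| Section 3 Concept sheet | -1 or earlier | baseline, no timing |
| 12.2 Flow cytometry timeline | -4 or earlier | not covered |
| 12.2 Need for multiple biopsies | not covered | before exposure |
| Section 13 rule | before start | before start |
| Table 7 calendar | pre-study, not C1D1 | pre-study, not C1D1 |

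Item 2 permits 9 daily offsets for blood (-7 to +1). The Concept sheet excludes 2 of them (0 and +1). The flow cytometry timeline excludes 5 (-3 to +1), leaving -7 to -4. Those two sources also disagree with each other: at least 1 day against at least 4 days before.

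**2. Effect on the measured CEC decline (illustration)**

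Let d be the true decline from pre-dose to day 8, and f the share of the log-decline already present at the baseline draw. The protocol gives neither. Then

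measured decline = 1 - (1 - d)^(1 - f).

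The value f = 1/7 is a log-decline spread evenly over seven days and sampled after one; 0.25 and 0.5 assume a faster early effect.

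| True decline d | f = 1/7 | f = 0.25 | f = 0.5 |
|---|---|---|---|
| 15% | 1 - 0.85^(6/7) = 13.0% | 1 - 0.85^0.75 = 11.5% | 1 - 0.85^0.5 = 7.8% |
| 20% | 1 - 0.80^(6/7) = 17.4% | 1 - 0.80^0.75 = 15.4% | 1 - 0.80^0.5 = 10.6% |

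The 10% cut-off is missed when f > 1 - ln(0.9)/ln(1 - d). That is 0.352 for d = 15% and 0.528 for d = 20%. At f = 1/7, only true declines between 10% and 1 - 0.9^(7/6) = 11.6% are reclassified.

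**3. The opposite direction**

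If CECs rise briefly by a fraction r at the time of the draw, the measured decline is 1 - (1 - d)/(1 + r). With r = 0.10 and d = 5% this is 1 - 0.95/1.10 = 13.6%, so a true decline below the cut-off reads above it.

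**4. Biopsy contrast**

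A biopsy two days after the start is on D3. Compared with D8, it spans 8 - 3 = 5 days of treatment, where a pre-dose sample would give 8 - 1 = 7.

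**The case against.** The strongest reply is that the flow cytometry timeline is the CEC-specific rule and section 12.2 item 2 is a general tube list. If the specific rule governs, no CEC denominator is on drug. The Summary, the Concept sheet, section 13 and the calendar all show the same pre-dose intent, so this may be a stray phrase. That argument stands as far as it goes, but the protocol states no order of precedence. A draw on the day after the start complies with the collection instruction, which is the text that names the flow tube. The flow cytometry timeline also gives no protection to the ELISA or biopsy baselines.

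A reader might infer that an active dose will be made to look inactive and that the Stage 1 dose choice is therefore biased. The documents do not support this:

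- The cut-off is lost for a true 15% or 20% decline only if more than about a third or a half of the day 8 effect appears within one day. The protocol's only timing statement, for gene expression, is that changes are present by day 6.
- The direction is open, as the transient-rise case shows.
- The way the 10% rule enters dose assignment is in Figure 2, which is not shown, and section 15 describes posterior estimates that are continuously updated.
- A different share of late baselines at different dose levels is possible, but nothing in the document indicates it.

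A reader might also put the biopsies 3 days apart. That requires a D6 sample, which comes from the tolerance on the day 8 visit and not from the baseline window.

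**Conclusion.** The point holds as an internal contradiction that is wrong as written. Section 12.2 allows baseline blood up to 1 day and baseline tissue up to 2 days after treatment starts. For blood this conflicts with the Summary, the Concept sheet, the flow cytometry timeline, and section 13 with its calendar. For tissue it conflicts with the Summary, the biopsy rationale, and section 13 with its calendar. The consequence is that the denominator of a Stage 1 primary endpoint can be an on-treatment value; it is not shown that it will be.

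Neither the size nor the sign of any bias can be derived from the protocol. The figures rest on assumed values of f, d and r. They show only that the effect could range from negligible to enough to cross the cut-off, in either direction. The one consequence fixed by the windows themselves is that the biopsy contrast can shrink from 7 to 5 days of treatment.

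**What to change.** - In section 12.2, Sample collection, items 1 and 2, end both baseline windows before the first dose by removing the allowances of 2 days and 1 day after the start.
- Reconcile the lead time for baseline blood across the Concept sheet, item 2 and the flow cytometry timeline into one pre-dose definition. The choice of lead time is the sponsor's; this review gives no ground for preferring 1 day, 4 days or another pre-dose limit.
- State that a sample taken after the first dose counts as a missing baseline in the Stage 1 dose-finding model and in all paired serum, tissue and expression analyses.

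The text change is a few sentences and touches no dose or treatment rule. The cost is that any patient sampled late loses a usable baseline. The protocol does not say how many that would be, and with 20-30 patients in Stage 1 each loss counts, so sites need to schedule the pre-dose draw and biopsy firmly.

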### Flow cytometry procedure

#### Timeline for doing flow cytometry

All patients would undergo serum CEC/EPC at least 4 day before administration of oral therapy, then at at D8 (+/- 2 days) , D30 (+/- 5 days), 30 days interval for first 3 months (+/- 7 days) and at progression.

#### Procedure

Collection of blood sample : 5 ml of blood sample from peripheral vein in EDTA vacutainer ( first 2-3 ml would be discarded )

#### Processing of sample

The blood would be processed within 24 hours of collection preferably within 4 hours

**Dilution of blood** : If TLC count is more than 20,000 per microliter than dilution would be used.

If not than then the whole blood with dilution would be subjected to further steps

**Blocking serum ( to inhibit nonspecific antibodies)** : Fc receptor blocking agent incubation for 30 min ( The amount and time would vary according to the kit)

**Incubation with monoclonal antibodies tagged with fluorescence** : 4 degree , 30 min in a dark place (The amount and time would vary according to the kit)

1. CD 146 ( endothelial cell marker, marker also seen on T cells)
2. CD 45 ( Antigen present on T cell but not on endothelial cells)
3. CD 34 ( endothelial and stem cell marker)
4. CD 31 ( Endothelial cell marker but absent in stem cell)

5. CD 133 ( progenitor cell marker)
6. Viability stain (7 AAD) ( apoptosis marker)

**Wash and red blood cell lysis** : Add 2 ml of NH4CL freshly prepared. ( 1X NH4CL=1800 microliter D.water + 200 microliter 10 X NH4CL)

**Run in Flow cytometer** : Instrument for Flow cytometry; 4-6 colour Flow cytometer, FACSCalibur ( Becton & Dickinson, USA)

#### Interpretation of results

1. 1 million events would be recorded
2. Debris and nonviable cell will be excluded by gating in FSC and SSC plot for 7 AAD
3. Gates would be drawn so that CD 146 + and CD 45 (-/dim) would be selected for further analysis
4. This gated population would be further subjected to gating for selection of CD 34 (+), CD 31 (+) cells
5. These cells would than be gated for CD 133
6. The population of CECs and EPC will be identified as per below
  - a. CECs : CD 146 (+), CD 45 (-/dim), CD 34 (+), CD 31 (+) and CD 133 (-)
  - b. Endothelial progenitor cells : CD 146 (+), CD 45 (-/dim), CD 34 (+), CD 31 (+) and CD 133 (+)
  - c. Cut off value for CD31 (+) would be kept at  $4 \times 10^1$  and at  $1 \times 10^1$  for 7AAD (+); CD146(+) and CD133 (+)

**Absolute number would be calculated by following formula = (Percentage of positive cells on total events ) / (TLC count)**

#### **ELISA**

##### Procedure

Collection of blood sample : 5 ml of blood sample from peripheral vein in EDTA vacutainer

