metronomic studies. An modification of this design with bayesian approach and CRM (continuous reassessment model) modelling has been developed and validated by Bhattacharjee et al. (Data sent for publication) It has been validated through data simulation of docetaxel patients where response rate and biomarker was used for decision making. This model takes into account 2 things, disease control (clinical factor) and proportional decline in circulating endothelial cells (biological factor). In the model proposed by Bhattacharjee et al rather than waiting for 3 patients at each dose level, bayesian approach with CRM modelling enables the users to use lesser number of patients and achieve the results early. In this design the efficacy details of each patient are feed into the model and then the model would predict whether the investigators needs to continue at the same dose level or de escalate the doses. The decision rules for the model can be seen in figure 2. This model uses both factors response to MCT and proportional decline in circulating endothelial cells for decision making. Interestingly though response has been used as primary deciding endpoint. In most of the scenarios especially in oral cancers metronomic chemotherapy leads to disease stabilization. In such cases using disease control rate as an criteria for metronomic chemotherapy seems more suitable. Disease control rate is an combination of complete response, partial response and disease stabilization. The variation in CEC measurement is to the tune of 10% or below hence we have used a proportional decline in CEC level of  $> 10\%$  as a deciding factor.

[figure not shown]

Figure 2 : Decision tree.

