### General Concomitant Medications and Supportive Care Guidelines

1. Loperamide for patients with Grade II or more diarrhoea following chemotherapy.
2. Doxycycline for patients with Grade II or more rash following chemotherapy
3. Topical steroids for patients with Grade II or more rash following chemotherapy
4. Oral steroid for patients with Grade II or more nausea or vomiting following weekly methotrexate

5. Antibiotics can be administered to patients presenting with febrile neutropenia as per the institute antibiotic policy.
6. Patients should continue pre-existing medications for other comorbid conditions. However the same should be noted for any significant interactions.

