## 15 Sample size calculation

**Total sample size** : Stage 1 ( 20-30 patients) + Stage 2 ( 76 patients). In stage the continuous reassessment model will be used hence the sample size would be maximum of 30 and minimum around 20. The exact calculations done in both stages are described below in details.

Stage 1 : Flexible-finite sample based approach will be adopted to select the circulating endothelial cells (CEC) interval boundaries and further to use optimum interval design. During the trial, we will continuously update the posterior estimates of decline in CEC and clinical benefit rate and assign patients to the most appropriate dose combination (Figure 1). The Bayesian adaptive screening design will be used to simultaneously select among possible treatment dose combinations. The design is based on formulating the selection procedure as a Bayesian hypothesis testing problem in which the superiority of each treatment combination is equated to a single hypothesis. During the trial conduct, we intend to use the current values of the posterior probabilities of all hypotheses to adaptively allocate patients to treatment combinations. The dose-finding decision will be decided on the twin endpoints the clinical benefit rate at 2 months and proportional decline in CEC at D8 of first cycle. Figure 2 will be used for decision making.

Stage 2: It was assumed that the 3-month progression-free survival (PFS) rate of a standard cancer therapy is 0.50 (H0). An improvement to 0.60 would be considered clinically significant (H1). Assume both the null and alternative PFS distributions follow an exponential distribution. The 1-sided type I error rate of 0.05 and type II error rate of 0.1. Prior assumption includes a fixed enrollment rate of 3 patients per month. We require a stop of 3 months at the end of Stage 1. The library("OptInterim") has been used to calculate the sample size. A 20%extra patient would be taken to account for lost to follow up data. Hence **a total of 76 ( 63 patients +13 patient) sample size is found suitable to carry out the study for stage II with single arm drug therapy.**

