## 16 Outcome measures

### 16.1 Primary outcome :

In stage I the OBD of methotrexate would be identified using response assessment criteria RECIST version 1.1 and flow cytometry measurement of CEC. So a twin primary endpoints of clinical benefit rate at 2 months ( CR or PR or SD persisting till 2 months) and proportional decline in CEC will be used for determination of OBD.

In stage 2 the PFS would be measured in days from date of recruitment in the study till the date of progression (clinical or radiological or both). Median PFS would be estimated by Kaplan Meier survival method.

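### The absolute CEC formula divides by the leucocyte count where it should multiply; the Stage 1 dose rule is affected if the CEC decline is computed from it, which the protocol does not say

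*Protocol*

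**What the plan says.** At the end of the flow cytometry procedure in section 12.2, after the gating steps that define CECs and endothelial progenitor cells, the protocol gives one rule for turning the result into a number: "Absolute number would be calculated by following formula = (Percentage of positive cells on total events ) / (TLC count"). The gating steps state that "1 million events would be recorded", so the percentage is taken on total acquired events. TLC is in cells per volume, as the sample-processing step shows: "If TLC count is more than 20,000 per microliter than dilution would be used".

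CEC also drives Stage 1. Section 15 bases the dose-finding decision on "the clinical benefit rate at 2 months and proportional decline in CEC at D8 of first cycle". Section 16.1 says that the twin endpoints of clinical benefit rate and "proportional decline in CEC will be used for determination of OBD". Section 4.7 adds the threshold: "we have used a proportional decline in CEC level of" more than 10%, chosen because measurement variation is put at 10% or below. None of these sections says whether the decline is taken on the absolute number or on the gated percentage.

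**The concern.** An absolute count is the fraction of positive cells times the number of cells per microlitre. The printed rule divides instead. A constant scaling error would cancel when D8 is compared with baseline, but this one does not, because TLC can differ between the two draws and it acts in the wrong direction. A fall in TLC pushes the computed CEC up, and a rise pushes it down.

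At stake is one of the two Stage 1 endpoints, if it is computed from this number. The methotrexate dose chosen in Stage 1 is the one carried into Stage 2. CECs are also named as pharmacodynamic endpoints for the PK-PD model (section 7.2), again without stating the scale.

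**Working it through.** **Inputs from the protocol.** Formula: percentage on total events divided by TLC (12.2). TLC per microlitre (12.2). Decision threshold: decline of more than 10% (4.7), assessed at D8 of cycle 1 (15).

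**Inputs not in the protocol.** No CEC percentages and no baseline or D8 TLC values are given. All values below are assumed, for illustration only.

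**Step 1: units.** Percentage / (cells per µL) has units of µL per cell, so it is not a number of cells. Percentage / 100 × (cells per µL) has units of cells per µL. With an assumed CEC percentage of 0.01% and TLC of 8000/µL:
- count: 0.01 / 100 × 8000 = 0.8 cells/µL
- printed formula: 0.01 / 8000 = 1.25 × 10⁻⁶

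**Step 2: change from baseline.** Let rp = CEC% at D8 / CEC% at baseline, and rT = TLC at D8 / TLC at baseline.
- count: D8/baseline = rp × rT
- printed formula: D8/baseline = rp / rT = (rp × rT) / rT²

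The two are equal only if rT = 1. On the log scale they are ln rp + ln rT and ln rp − ln rT. Their product is (ln rp)² − (ln rT)², which is negative, so the signs differ, whenever |ln rT| > |ln rp|.

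**Step 3: numbers.**

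| rp (assumed) | rT (assumed) | Count: rp × rT − 1 | Printed formula: rp / rT − 1 | Decline of more than 10%? Count / formula |
|---|---|---|---|---|
| 0.80 | 1.00 | −20.0% | −20.0% | yes / yes |
| 1.00 | 0.80 | −20.0% | +25.0% | yes / no |
| 0.90 | 0.90 | −19.0% | 0.0% | yes / no |
| 0.80 | 0.85 | −32.0% | −5.9% | yes / no |
| 0.50 | 0.75 | −62.5% | −33.3% | yes / yes |
| 1.00 | 1.25 | +25.0% | −20.0% | no / yes |
| 1.10 | 1.25 | +37.5% | −12.0% | no / yes |

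The first row shows that the error vanishes when TLC is stable. The fourth shows that the 10% rule can flip without a change of sign. The fifth shows that a large fall in the percentage can survive the error. The last two show an apparent decline when the count has risen.

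**Step 4: how small a TLC change matters.** The two ratios differ by the factor 1 / rT². For a 5% fall in TLC this is 1 / 0.95² = 1 / 0.9025 = 1.108, so the computed ratio is about 11% too high. That is about the width of the decision threshold.

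**Step 5: does the protocol foresee TLC movement?** Section 11.4 attributes haematological toxicity to methotrexate and schedules a hemogram around D8. Section 11.1 lowers the TLC floor from 3000 to 2000 per cumm after the first cycle. Section 21 lists leucopenia among the monitored events. Section 11.2 allows "Oral steroid for patients with Grade II or more nausea or vomiting following weekly methotrexate". So a change is foreseen as possible, but its size by D8 is not given.

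**The case against.** The strongest objection is that the link to Stage 1 is an inference. Sections 4.7, 15 and 16.1 speak only of a proportional decline in CEC, and section 16.1 refers to flow cytometry measurement, which fits the gated percentage as well. If the percentage is used, the formula never reaches dose selection. This stands. A reader might infer that the printed number is itself the Stage 1 endpoint. The documents do not say so, although no other rule for quantifying CEC is offered, which makes that reading plausible.

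A reader might also infer that the error hides CEC decline most at the higher methotrexate doses and so pushes the choice toward lower ones. That needs a dose-dependent fall in TLC by D8, and the protocol gives no TLC data at any dose level. D8 normally follows a single weekly dose, and section 4.7 holds that toxicity is not a concern with metronomic schedules. Selection also rests on clinical benefit at 2 months and on a decision tree whose figure is not available here. Neither direction nor size can be derived.

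The oral steroid provision covers only patients with Grade II or worse nausea or vomiting, which section 11.4 calls unlikely. It therefore shows only that TLC might rise in some patients.

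Finally, the division sign may be a typing slip, and a laboratory might notice values near 10⁻⁶. Nothing shows that any value was computed this way. This lowers the chance of harm but does not correct the instruction.

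**Conclusion.** The formula is wrong as written, in units and in direction, and this needs no assumption. Its effect on a D8/baseline comparison is exact: the ratio is too large by the factor 1 / rT² when TLC falls and too small by the same factor when it rises. It is zero when TLC is unchanged.

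The effect on Stage 1 is conditional. If the proportional decline is computed from this number, patients can be placed on the wrong side of the 10% rule: under the assumed TLC changes of −20% and +25% with an unchanged CEC percentage, the results are +25% instead of −20% and −20% instead of +25%. If the raw percentage is used, dose selection is unaffected. The documents do not support a claim that the selected dose is wrong or biased in a known direction. The same condition applies to the PK-PD model. The protocol should therefore correct the formula and also say which CEC quantity is the endpoint, since correcting the formula alone would leave the endpoint undefined.

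**What to change.** In section 12.2, replace the formula with: absolute CEC (or EPC) per µL = (percentage of positive cells / 100) × TLC per µL, times any dilution factor.

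Two details need wording:
- **Denominator.** The protocol's percentage is on total acquired events, while TLC counts leucocytes only. State a denominator that matches the leucocyte count. This is a change of definition and should be written as one.
- **TLC source.** Take TLC from the same draw as the flow sample. The scheduled hemogram does not guarantee this: on treatment its window is D7–D10, against D8 ± 2 days for flow. At baseline, bloods are due within one week of starting, against at least 4 days before therapy for flow.

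In sections 4.7, 15 and 16.1, state that the D8 proportional decline and the 10% rule use this absolute number, or state explicitly that they use the percentage. State the scale for the PK-PD model as well. Recompute any value already obtained by division before it enters the dose-finding model.

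The cost is a few sentences and a spreadsheet correction. No extra visit is needed, but a TLC must be run on the flow draw wherever the routine hemogram falls on another day.
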